### Data collection (effectiveness evaluation)

All primary and secondary outcomes will be assessed at baseline and at a 12-month follow-up. An online survey will be distributed during working hours.

#### Primary outcome

The primary outcome is *stress* assessed with three items (e.g. How often have you had problems relaxing?) preceded by “These questions are about how you have been during the last 4 weeks” from the Copenhagen Psychosocial Questionnaire (COPSOQ), version III [41]. COPSOQ covers a broad range of organizational and social work conditions. The instrument is well-established and was developed for use in occupational risk assessment and research on work and health. The response categories for the three stress items range from (1) “all the time” to (5) “not at all”.

#### Secondary outcomes

*Quantitative demands* assessed with three items (e.g. Do you get behind with your work?) from COPSOQ III with response categories ranging from (1) “always” to (5) “never/hardly ever”.

*Role clarity* assessed with three items (e.g. Does your work have clear objectives?) from COPSOQ III with response categories ranging from (1) “to a very large extent” to (5) “to a very small extent”.

*Psychosocial safety climate (PSC)* is assessed with four validated [42] items (e.g. Senior management considers employee psychological health to be as important as productivity). The response categories range from (1) strongly disagree to (5) strongly agree.

*Team effectiveness* is assessed with four items (e.g. How effective is your team in making use of the skills of the different team members?) from a scale developed by Maynard [43]. The response categories ranging from (1) “not good at all” to (5) “very good”. This scale has not been validated in Swedish.

*Planning* is assessed with one item (Do you experience the work at your workplace as well-planned?), previously used in a Swedish report [11] looking at the relation between serious workplace accidents and the work environment.

*Staffing* is assessed with two self-constructed items (e.g. Is the staffing at your workplace sufficient in terms of number of individuals?). The response categories ranging from (1) “to a very high extent” to (5) “to a very low extent”.

### Data collection (process evaluation)

*Fidelity* will be operationalized as adherence to the intervention. To assess this, we will ask all managers who are supposed to make the behavior change to rate to what extent they are undertaking the intervention components (specified behaviors) prior to the implementation and again after the project has finished. Hence, the intervention components are not completely new, rather they have a potential of improvement. To assess adherence to duties clarification and staffing we will use a questionnaire comprising 7 items (e.g. We have performed a duties clarification regarding the work tasks in the project). The questionnaire to assess structured roundmaking comprise 8 items (e.g. Structured roundmaking is a part of the weekly schedule for the first line manager). The response categories for both scales ranging from (1) “to a very high extent” to (5) “to a very low extent”. All items build on the company’s own standards for evaluation. In addition to this, one of the intervention components (structured roundmaking) will be assessed using observations. We will do this to minimize the risk of social desirability [44] as observation is a more objective and valid way of evaluating behavioral changes.

*Readiness for change* and *Support from managers* will be assessed using the validated Intervention Process Measure (IPM) [45]. Readiness for change will be assessed before the implementation. The measure consists of five subscales of which we will use two: line manager attitudes and actions (Support from managers*)* and employee readiness. Randall (2009) recommends tailoring of the items to the specific contexts, which we did by specifying the interventions (structured roundmaking and duties clarification). Hence, readiness for change is assessed with four items (e.g. “I am ready to accept the changes brought about by the implementation of structured roundmaking”). Support from managers is assessed with seven items (e.g. “My immediate manager was positive about the implementation of structured roundmaking”). The response categories range from (1) “strongly agree” to (5) “strongly disagree”, Likert-type scales.

#### Barriers and facilitators to adherence

This will be explored using semi-structured interviews with different stakeholders (e.g. managers supposed to employ the intervention components, senior managers, safety representative) during the intervention and at the end or after completion. Informants will be chosen from the intervention projects with the aim to get comprehensive and rich data from different levels within the company. Hence the sampling strategy will be stratified purposeful using the pre-defined criterias nested and multi-level [46]. Three to four informants within each district (a total of 4 districts) will be asked to participate in the qualitative study. A minimum of 12 informants will be included following the recommendations of Onwuegbuzie (2007).

*Dose* (the quantity of implementation strategies fulfilled) *and reach* (workers’ participation in the completed activities) will be documented using attendant lists and a logbook.

#### Risk of contamination

To assess whether and to what extent the control region works with improvements in the chosen intervention components we will conduct semi-structured interviews with relevant stakeholders from the control region. We will also study their business case for 2020 to investigate the control region’s objectives and activities regarding health and safety.

### Statistical methods (intervention effectiveness)

To evaluate the effect of the intervention we will examine between group differences over time. The analyses will consider the clustering of observations of workers within the working team (project), as well as the repeated measurements within each worker. Intention-to-treat analyses will be used and where relevant, compared to per-protocol analyses. Adjusted models will be applied if potential confounders are unevenly distributed and if this is likely to affect the results when the two groups (intervention and control) are compared.

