### Aim and objectives

The aim of this project is to contribute to the knowledge on how to change adverse working conditions within the construction industry by evaluating a co-created intervention with the aim to improve organizational and social working conditions, enhance team-effectiveness and decrease stress.

The primary objective is to compare the effectiveness of a co-created intervention versus standard procedures on role clarity, quantitative demands, staffing, planning, team effectiveness, psychosocial safety climate and stress (effectiveness evaluation).

The secondary objective is to evaluate the implementation process regarding fidelity (adherence to the intervention) and barriers and facilitators to adherence. This will be done using mixed methods, that is, both qualitative and quantitative methods will be used to collect data.

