## Methods

### Trial design

The study is a controlled trial with before and after measurements involving two regions (one intervention and one control region) and approximately 45 construction teams (projects). Randomization was not possible due to the fact that the intervention region wanted all groups (building projects) to receive the intervention. Instead we matched a control group (region). The criteria applied for matching were type of work (same branch) and region size (*N* > 300). Employees of the participating regions will be invited to complete outcome questionnaires during working hours at baseline and at 12 months follow-up. Our intention is to also include an 18-month follow-up questionnaire, however this has not yet been approved by the control region.

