#### Recruitment of regions

Two large construction companies in Sweden were contacted and after a few meetings one of them agreed to participate in the study. A short listing of eligible branches and regions was conducted in collaboration with representatives from the company. The building construction branch was chosen as the context for the intervention. The national manager of health and safety took on the responsibility to inform the regions about the study and look for potential participants. One region (employees = 360) applied to take part in the study with one condition, the whole region should be included in the intervention. Hence, this became the intervention group. The matched control region (employees = 450) accepted to participate after discussions in their highest management team.

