#### Sample size /power calculations

Since the size of the intervention and control region was given, we performed power calculations. However, since the outcomes were chosen through co-creation later in the process we elaborated with different mean differences (5, 7, 9 and11) and different standard deviations (SD) 10, 15, 20 and 30. Based on a level of significance (α) of 0.05, results show a desired statistical power (1-β) of 0.9 given a mean difference of 5 and a SD not higher than 15. A SD of 20 with the same mean difference gives a statistical power (1-β) of 0.8. Given a higher mean difference between the intervention and control group, power increases, even with larger standard deviations. A mean difference of 9 and a SD of 30 gives a statistical power (1-β) of 0.8.

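### With one region per arm, the project-clustered analysis supports inference about these two regions only; read as evidence of effectiveness, its intervals omit any region-level difference in change

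*Protocol article*

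**What the plan says.** Under Trial design, the Protocol article describes a controlled trial "involving two regions (one intervention and one control region) and approximately 45 construction teams (projects"), and explains: "Randomization was not possible due to the fact that the intervention region wanted all groups (building projects) to receive the intervention". Recruitment of regions adds how each arm came about: "One region (employees = 360) applied to take part in the study with one condition, the whole region should be included in the intervention", and "The matched control region (employees = 450) accepted to participate after discussions in their highest management team". Matching used branch and region size only.

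The intervention is also run regionally. Under Intervention development and planning, the regional manager is project owner, and the activities were written into the region's 2020 business case.

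Under Statistical methods, the contrast is "To evaluate the effect of the intervention we will examine between group differences over time", and the dependence structure is "The analyses will consider the clustering of observations of workers within the working team (project), as well as the repeated measurements within each worker". Region is not named as a source of variation. Aim and objectives frames the target as effectiveness: "The primary objective is to compare the effectiveness of a co-created intervention versus standard procedures". The Discussion lists selection bias from non-randomization and possible contamination as limitations. It does not say that intervention and region coincide, or that the error bars leave out between-region variation.

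**The concern.** Arm and region are the same variable. Anything that moves one whole region differently from the other between baseline and 12 months, such as a shift in its order book or a local event, enters the estimated effect in full and adds nothing to the standard error. The about 45 projects serve as the independent units, although the intervention was given to one region as a block.

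What is at stake is the meaning of the primary stress result. A significant project-clustered test shows that stress changed differently in the two regions. To read it as a 5% test of the intervention also requires that the two regions would otherwise have changed by the same amount, and the trial data cannot check that.

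**Working it through.** The article gives no standard error, interval width, ICC or between-region variance, so there is no figure of its own on this point to reproduce. Its power figures are a separate matter and are used only as a source for the SD and the difference.

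**Inputs from the Protocol article**
- Regions: 1 per arm, with 360 and 450 employees (Recruitment of regions).
- Projects: about 45 (Trial design).
- SD 20 and mean difference 5: one scenario under Sample size / power calculations.
- Significance level: "Based on a level of significance (α) of 0.05". Sidedness is not stated; two-sided is taken here.

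**Assumptions**
- Project ICC 0.05.
- 18 workers per project, from (360 + 450)/45 = 18. This counts some staff who are excluded or work outside projects.
- Full response, with 50% response as an alternative.
- SD 20 is the SD of the analysed quantity. A repeated-measures model would give a different standard error, depending on a within-worker correlation that is not given.
- s, the SD of region-level change unrelated to the intervention, in the units of the power calculation. No value is given in the article.

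**Region-level degrees of freedom:** 2 regions − 2 arms = 0. A region random effect cannot be separated from the arm effect.

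**Model standard error, full response**
- Design effect = 1 + (18 − 1) × 0.05 = 1.85.
- SE² = 20² × 1.85 × (1/360 + 1/450) = 400 × 1.85 × 0.005 = 3.70, so SE = 1.92.
- 95% half-width = 1.96 × 1.92 = 3.8.

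**Adding region-level change.** Each arm contributes one region, so total variance = SE² + 2s². The actual error of the nominal test is 2 × [1 − Φ(1.96 × SE / total SE)].

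| s | Total SE | 95% half-width | Actual error |
|---|---|---|---|
| 0 | 1.92 | 3.8 | 5.0% |
| 0.25 | √3.825 = 1.96 | 3.8 | 5.4% |
| 0.5 | √4.20 = 2.05 | 4.0 | 6.6% |
| 1 | √5.70 = 2.39 | 4.7 | 11% |
| 2 | √11.70 = 3.42 | 6.7 | 27% |
| 3 | √21.70 = 4.66 | 9.1 | 42% |

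**At 50% response** (180 versus 225, 9 per project): design effect = 1 + 8 × 0.05 = 1.40, and SE² = 400 × 1.40 × 0.01 = 5.60. For s = 1, 2 and 3 the error is about 9%, 21% and 34%. The inflation is smaller because the model standard error is already larger.

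**With project ICC 0.02** (18 per project, full response): SE² = 400 × 1.34 × 0.005 = 2.68. For s = 1 and 2 the error is about 14% and 33%.

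**Tipping point for an observed difference of 5, full response, ICC 0.05:** significance is lost when total SE = 5/1.96 = 2.55. Then s = √((2.55² − 3.70)/2) ≈ 1.2 points.

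**The case against.** The strongest reply is that this is a limit of the design rather than a mistake in the model. Project clustering plus repeated measures is the structure that can be estimated, and it is valid for comparing these two regions. No other model would recover region variance from one region per arm. That stands, so the Statistical methods section is not wrong in the model it names; what needs changing is the inference drawn from it.

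The article also does more than admit selection bias. It states openly that there is one region per arm. Both regions belong to the same company and branch and exceed 300 employees, which may limit divergence. The change-over-time contrast removes stable regional differences, and uneven confounders may be adjusted for. Control-region interviews and its 2020 business case will be examined, and fidelity, dose, reach and context are measured. All of this helps interpretation. None of it supplies the missing variance, and matching on branch and size does not ensure equal change.

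Nor is every regional shift a nuisance. Staffing is a targeted outcome, and management support is part of the implementation, so some such change may be the intended effect.

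Three stronger readings are tempting and are not supported:
- A reader might infer that the test's true error rate is 11% to 42%. Those figures rest on s = 1 to 3, for which the article gives no basis; at s = 0.25 or 0.5 the inflation is slight.
- A reader might infer that the intervals are too narrow without qualification. That holds only for inference to the intervention's effect, and only if region-level change differs for other reasons.
- A reader might infer that effectiveness may be claimed only if the result survives some fixed s. Nothing in the article justifies a particular value, so such a threshold would be arbitrary.

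A separate statistical analysis plan may contain a sensitivity analysis, and its absence from the article is not held against the trial. No such plan can create region-level degrees of freedom, so the point about what may be concluded remains.

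**Conclusion.** The point holds as a limit on inference. With one self-selected region per arm, the planned interval and p-value answer whether stress changed differently in these two regions. They carry nominal error rates for the effectiveness of the intervention only if region-level change unrelated to it is exactly equal in both. Any departure makes them too narrow; that direction does not depend on the assumed inputs.

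The size cannot be known from the article. Under the illustrative inputs it runs from negligible (s of 0.25 to 0.5) to serious (s of 2 to 3). A 5-point difference, the smallest in the power scenarios, would stop being significant at s of about 1.2, which is 6% of the assumed SD of 20 (1.2/20). The ICC, cluster size, response rate and s are all assumptions.

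This should be fixed. It does not invalidate the trial or its estimable model, but it determines how the primary result may be worded.

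**What to change.** - **Statistical methods:** state that the project-clustered interval is conditional on these two regions and excludes between-region variation in change.
- **Sensitivity analysis:** before the outcome data are analysed, specify that 2s² will be added to the variance of the stress effect over a range of s starting near zero. Report the s at which the result loses significance, with no pass/fail threshold attached.
- **Primary conclusion:** word it as a difference in change between two regions, interpreted together with the process evaluation and the contamination data from the control region.
- **Discussion:** add to the limitations that intervention and region are fully confounded, as a point distinct from selection bias.

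This needs no new data, outcome or model: one further calculation and a few sentences. The price is a wider sensitivity interval beside the main one and a more cautious claim.

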### Qualitative analysis (interviews and observations)

Regarding the qualitative data we will perform thematic analysis [47]. The interviews and the observations will be digitally recorded an transcribed verbatim. Field notes from the observations will also be included in the analysis. The first step of the analysis will be to listen to the recordings and read through notes and transcripts to familiarize with the data. A data-driven coding process will follow, which is performed by two investigators independently. The coding will set the ground for the initial theme creation, which will then be discussed in the research group to enhance credibility. To further understand the data and highlight findings the researchers, if found appropriate, will revisit the literature (theory) and employ an iterative process between the data and the literature (theory) according to the tin-opener approach [48].

## Discussion

This paper outlines the design of a controlled trial testing the effectiveness of a co-created behavior change intervention with the aim to improve organizational and social working conditions, team effectiveness and decrease stress. To the best of our knowledge not many primary organizational-level intervention studies with the aim to improve organizational and social working conditions and decrease stress have been conducted within the construction industry. With this study we wish to add to the scientific literature with knowledge about how adverse psychosocial working conditions can be improved within the construction industry.

Given the importance of making the intervention fit to the context, discussed in earlier research, our intention was to, instead of viewing interventions as discrete packages of components isolated from their contexts [31], include the system into which we wanted to introduce change in our intervention. Another factor described in the literature to be important for the success of interventions is to let the receivers of the intervention participate in designing it and deciding on its content. Most interventions within the literature are described as participatory, however a clarification of in what way the intervention is participatory is often lacking [29]. Given the importance of a contextual fit and a participatory approach we chose to focus on co-creation as a means to reach these goals. In practice this meant that representatives from the studied organization (end-users and providers) were invited to discuss and decide, not only the content (intervention components) but also the process (implementation strategies). In line with recommendations in the literature [23, 40] we carefully selected and defined the implementation strategies suitable for the identified barriers and facilitators [23, 40]. In sum, we believe that by designing an intervention study with co-creation of the logic model and implementation strategies, we have taken thorough action in order to avoid implementation failure, which has been proposed to be of high priority for success with intervention studies [23].

One limitation is the possible risk of selection bias because randomization was not possible. It is likely that the included intervention group represents a motivated group with a high interest in improving the psychosocial work environment as they volunteered for the study. Co-creation also has its benefits and constraints. The research group somewhat loses control, in this study over the outcomes and intervention components selected, as it is in the nature of co-creation to let the end-user prioritize this. In this study the choice of intervention components fell on improving core tasks, rather than testing new routines. This implies a risk of contamination between the intervention and the control group. However, this will be monitored using interviews with relevant stakeholders within the control region, keeping track of whether, and if relevant how, they are focusing on improving the same routines.

The study also has several strengths. First, the co-creation of the outcomes, intervention components and the implementation strategies have enhanced the fit into the context and ensured a buy-in from senior management. The fact that the outcomes and the intervention components have been included in the business case for 2020 enhances the possibility that the project will be prioritized. It is, to our knowledge, the first time this is done in an occupational health organizational-level intervention study. Furthermore, the structured approach to identifying barriers and facilitators and thereafter choosing theory-driven (COM-B) implementation strategies is a recommended procedure [26]. Last, the evaluation of both effectiveness and the implementation process is a recommended and preferable strategy [21] in order to be able to understand why (or why not) and in what way the intervention was effective.

## Data Availability

The datasets generated and analyzed during the current study are not publicly available due to legal restrictions.

